## Abstract

**Background:**

The prevalence of mental health disorders is increasing globally, and the prevalence of COVID-19 has made it worse. Evidence has indicated a major mental health burden and elevated anxiety associated with the new coronavirus outbreak in the general population. This study aims to evaluate an evidence-based web application (Naranj) for stress management among Iranian college students.

**Methods and design:**

This study aims to present a protocol related to a randomized controlled trial among Iranian college students. The study will be conducted on 100 students from two colleges of Shiraz University of Medical Sciences in Iran. The participants will be randomly assigned to the intervention and control groups. The intervention group participants will be provided with a web application, whereas the control group ones will be provided with an app unrelated to stress management. The primary outcome for this study will be the Perceived Stress Scale, and the two groups will be compared with respect to stress level and sleep quality.

**Discussion:**

A web application will be developed according to psychological theories and will be scientifically approved for managing college students’ stress and improving their sleep quality during the COVID-19 outbreak.

**Trial registration:**

Iranian Registry of Clinical Trials IRCT20160427027647N2. Registered on 14 May 2020

## Background

A new infectious respiratory disease, named COVID-19, appeared in Wuhan, Hubei province, China, and it has affected almost all other countries throughout the world. According to the World Health Organization (WHO, 6 July 2020), COVID-19 has affected over 11,327,790 people and has killed 532,340 people in more than 200 countries worldwide [1]. A study found that similar to the SARS-induced psychological burden [2], anxiety symptom levels increased when COVID-19 occurred in China [3]. Moreover, initial studies indicated a major mental health burden among the public, increased depressive symptoms, decreased sleep quality, and elevated anxiety during the COVID-19 outbreak [3–5]. In this regard, a study in China revealed that stress, anxiety, and depression were more prevalent among students and healthcare professionals in comparison with other professions [6]. Moreover, another study showed that Chinese young people and those who spent more time thinking about COVID-19 were more at risk [3]. The probable cause of mental health problems during the coronavirus pandemic could be related to the “hypochondria concerns” theory that means being worried about being infected [7]. According to a Spanish study, it could also be related to important life changes in a very short period of time, including changes in financial or occupational status, restrictions on movement, and cancelation of important activities [8].

In general, the prevalence of mental disorders is increasing globally [9]. Statistics have shown that about 970 million people worldwide suffered from some sort of mental illnesses in 2017 [10], 75% of whom lived in low- and middle-income countries [11]. Mental health problems are one of the main causes of the global disease burden, such a way that they account for 13% of the total global burden of disease [12]. Mental illnesses also account for 25.3% and 33.5% of all years lived with a disability in low- and middle-income countries, respectively [12]. According to the latest Ministry of Health nationwide study regarding mental health disorders in Iran in 2015, about 23.4% of the population were suspected to suffer from a kind of mental disorder. According to this report, about one out of every four people was suspected to suffer from mental disorders [13]. These results were in line with the global average [14].

It has been claimed that the prevalence of anxiety and depression has increased by about 40% over the past 30 years [15]. It has also been estimated that around 4% of the population had an anxiety disorder [16]. In addition, stress has been classified as the health epidemic of the twenty-first century by the WHO [17]. Stress has been defined as the body’s response to painful situations that cause discomfort, which can lead to depression and health problems [18]. In Iran, limited research has been conducted in this field among the general population. The results of a study conducted among the people aged 18 years in Tehran (2017) showed that more than 80% of the people had experienced at least one severe episode of stress during the past year [19]. The results of another study conducted on 10,000 adult residents of Yazd Province revealed that 34.8% of the people had experienced stress [20]. Furthermore, previous research showed that college students had experienced high levels of stress. Studies have also reported some levels of stress and anxiety among students in China (74.3%), Saudi Arabia (63.5%), Bangladesh (61%), and Egypt (59.9%) [21–24]. A case report performed in Iran also indicated that 83% of the students had experienced stress [25]. The most common stressors among the students were parental expectations, university/life balance, financial/work balance, living away from home, sleeping difficulties, and academic issues [26, 27].

Stress can lead to serious health problems and can damage almost all body systems [28]. Studies have found that stress was associated with an increased risk of rheumatoid arthritis [29], cardiovascular disease [30], cancer [31], and autoimmune diseases such as systemic lupus erythematosus, type 1 diabetes, and multiple sclerosis [32].

Despite the importance of mental health problems, WHO reported that nearly two thirds of people with a known mental health problem never sought professional help. It was also stated that stigma, discrimination, and ignorance prevented people from receiving treatment and care [10]. Therefore, societies should provide people with an easy, inexpensive, affordable, and reliable way to access medical services remotely. Digital technology initiatives, such as m-Health, could be helpful in this regard. M-Health refers to the utilization of mobile phones and other wireless technologies in medical care. Some studies have shown evidence supporting the effect of m-Health on different fields of health [33–35]. The good news is that from more than 15,000 mobile apps, at least 29% have been designed in the field of mental health [36]. The bad news is that a small number of apps are evidence-based [37]. Besides, a study that appraised mental health apps showed that only few of them could be personalized [38]. Moreover, the results of a study demonstrated that more than 50% of students reported low levels of eHealth literacy [39]. Therefore, users have to be empowered to use digital technologies effectively.

The results of a survey revealed that college students had higher anxiety levels compared to the general population after the outbreak of COVID-19. This implied that COVID-19 had negative psychological impacts on Chinese college students’ anxiety levels [40]. Considering the spread of mental health problems and the prevalence of COVID-19 that has made it worse, it is necessary to take appropriate and timely measures. In this context, mental health support should be provided and continued for all people, especially the vulnerable groups. Such support should include accurate information as well as training of suitable coping strategies to manage the situation. Therefore, the present study aims to evaluate an evidence-based web application (Naranj) for stress management among Iranian college students during the COVID-19 outbreak. It has been hypothesized that the application is effective in decreasing college students’ psychological stress. The secondary expected outcome is the improvement of sleep quality.

## Methods/design

### Aims and objectives

This study aims to assess the efficacy of a web application (Naranj) for stress management among Iranian college students during the COVID-19 outbreak.

### Design and setting

This is a non-blind, parallel-group (ratio 1:1), randomized controlled trial (superiority framework). The participants will be recruited from two colleges of Shiraz University of Medical Sciences in Iran: (1) School of Management and Medical Information (Health Information Management, Medical Informatics, and Health Services Management) and (2) School of Health.

### Sample size

The sample size is calculated based on a similar previous study [41] where the mean (SD) of perceived stress in groups 1 and 2 were 7.43 (2.93) and 9.49 (3.06), respectively. This study was a research aimed to evaluate the efficacy of a stress management app for college students. We chose this randomized controlled trial study because it was very similar to our study in terms of the intervention, outcome, and participants. After that, the sample size is calculated using the NCSS software. The minimum sample size based on power = 80%, and *α* = 0.05 is estimated at 35 individuals in each group. In order to compensate for the loss to follow-up, we will increase the sample size to 50 individuals in each group.

### Participants

#### Inclusion criteria

Students will have to meet the following eligibility criteria to be included in the study: (1) aging 20–35 years; (2) being a BSc (second and higher semesters) or an MSc student; (3) having a smartphone, computer, laptop, or tablet; (4) not suffering from known psychological problems; (5) not consuming psychiatric drugs; (6) not being addicted according to the students’ self-expression; (7) not having chronic physical diseases (including diabetes, hypertension, hypothyroidism, hyperthyroidism, asthma); (8) not having physical disabilities (including blindness and deafness); (9) being willing to participate in the study; and (10) signed informed consent forms.

**Fig. 1 Fig1:**
[figure not shown]
The participants’ timeline

#### Exclusion criteria

The students will be excluded if they are not willing to take part in the research.

### Randomization

The participants will be selected by the systematic random sampling method based on two separate lists of all eligible BSc and MSc students in both colleges. We will select 50 students at each college. Then, the selected students will be provided with an explanation of the aims and scope of the project and will be orally invited to participate in the research. If they accept the invitation, they will be asked to sign informed consent forms. However, if they do not give informed consent, the next student in the systematic random sampling list will be substituted. Then, we will allocate the participants of each college into 2 groups of intervention and control based on two separate 1:1 permuted block randomization lists, so that five blocks of size 10 in each college will be formed. The randomization sequence will be generated by the biostatistician using the Random Allocation Software with a 1:1 allocation. Assigning participants to their groups will be carried out via random allocation.

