### Statistical analysis

The Kolmogorov-Smirnov test will be used to test the normal distribution of the data. The comparability of the intervention and control groups will be assessed at baseline. The quantitative variables will be described using mean and standard deviation if they follow a normal distribution and using median and range in case of non-normal distribution. The qualitative variables will be presented as percentages and confidence intervals. In order to compare the study groups regarding the mean scores of stress and sleep quality, the independent samples *t* test will be applied. In addition, the Mann-Whitney *U* and chi-square tests will be used to compare the two groups regarding non-parametric and categorical variables, respectively. In case of confounders, analysis of covariance or linear regression model will be used. Moreover, the paired samples *t* test will be utilized in order to compare the mean scores of stress and sleep quality in each group. Intention-to-treat analysis will be employed, as well. All analyses will be conducted using the SPSS 16 software, and *p* ≤ 0.05 will be considered statistically significant.

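### Randomisation is stratified by college but the named between-group tests ignore college, which costs some precision if stress or sleep scores differ between the two colleges

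*Protocol article*

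**What the plan says.** Under Randomization, the protocol article states "We will select 50 students at each college". Each college's participants are then allocated "based on two separate 1:1 permuted block randomization lists, so that five blocks of size 10 in each college will be formed". This is randomisation stratified by college, with blocks inside each stratum.

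Under Statistical analysis, the groups are compared as follows: "regarding the mean scores of stress and sleep quality, the independent samples *t* test will be applied". For other kinds of variable, "the Mann-Whitney *U* and chi-square tests will be used to compare the two groups regarding non-parametric and categorical variables". Covariate adjustment is conditional: "In case of confounders, analysis of covariance or linear regression model will be used". College is not named there, and nothing else in the article says that the analysis will reflect the stratified allocation.

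**The concern.** When arms are balanced inside each college, any difference in mean score between the colleges cancels out of the arm contrast. The true sampling variance of the treatment difference then contains only within-college variation. The independent samples t test pools the variance within each arm across both colleges, so its error term still holds the between-college part. The Mann-Whitney test has the same feature on the rank scale.

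If college is related to the outcome, the analysis therefore does not match the design: the confidence interval is wider than it needs to be, the true type I error is below the nominal 5%, and some power is given away. What is at stake is precision. The estimated difference stays unbiased under balanced allocation, and false positives are not inflated.

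**Working it through.** **Inputs from the protocol article**
- Randomization: 50 students per college, five blocks of 10 at 1:1. That gives 5 × 5 = 25 per arm in each college and 50 per arm overall.
- Sample size: "the mean (SD) of perceived stress in groups 1 and 2 were 7.43 (2.93) and 9.49 (3.06), respectively". The difference is 9.49 − 7.43 = 2.06. The pooled SD is sqrt((2.93² + 3.06²)/2) = 2.996. The standardised effect is 2.06/2.996 = 0.69.
- Sample size: 80% power, α = 0.05 (two-sided assumed), at least 35 per group, raised to 50 for loss to follow-up.

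**The plan's own figure.** With a noncentral t calculation, power is 79.8% at 34 per group and 80.9% at 35, so the stated 35 reproduces. At 50 per group power is 92.6%. The sample size is not in dispute.

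**Assumed input.** The article gives no difference in PSS or PSQI between colleges. Let R² be the share of within-arm outcome variance due to college. With two equal colleges a gap of g SDs gives R² = g²/4, so R² of 1%, 5%, 10% and 20% means gaps of 0.20, 0.45, 0.63 and 0.89 SD.

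**Standard error.** With n per arm and total SD σ:
- the t test uses σ·sqrt(2/n);
- the true value under balance within college is σ·sqrt(1 − R²)·sqrt(2/n);
- the ratio is 1/sqrt(1 − R²).

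**Type I error at 50 per arm.** The t test rejects when |t| exceeds 1.984 (98 df). On the correct scale the cut-off is 1.984/sqrt(1 − R²), referred to t with 97 df.

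| R² | SE ratio | Effective cut-off | Type I error |
|---|---|---|---|
| 0 | 1.000 | 1.984 | 0.050 |
| 1% | 1.005 | 1.994 | 0.049 |
| 5% | 1.026 | 2.036 | 0.044 |
| 10% | 1.054 | 2.092 | 0.039 |
| 20% | 1.118 | 2.219 | 0.029 |

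Simulation of the design agrees with these to within about 0.001. With college in the model, simulated type I error stays at about 0.05 throughout.

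**Power at the protocol's effect** (simulated; difference 2.06, total SD held at 2.996). The 34-per-arm rows have 17 per arm in each college, the nearest even split to the planned minimum of 35.

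| Per arm | R² | Without college | With college | Loss (points) |
|---|---|---|---|---|
| 50 | 5% | 93.0% | 93.7% | 0.7 |
| 50 | 10% | 93.6% | 94.9% | 1.3 |
| 50 | 20% | 94.6% | 96.8% | about 2 |
| 34 | 5% | 80.3% | 81.7% | about 1.4 |
| 34 | 10% | 81.0% | 83.8% | about 3 |
| 34 | 20% | 82.4% | 87.9% | about 6 |

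At R² of 1% and 50 per arm, the loss is 0.1 to 0.2 points.

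**The case against.** The strongest reply is that the harm may be nil. Both colleges are health-related schools of one university, with the same eligibility rules, and nothing in the article suggests that their students differ in stress or sleep. For a gap of 0.2 SD the effect is negligible. This stands, and it is why the size can only be given as a range that includes small values.

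A second reply is that the plan already allows analysis of covariance or regression, and that the choice of covariates is commonly left to an SAP, which is not shown here. This mitigates the point but does not answer it. The clause is triggered by confounding, and a factor balanced between arms by design would not normally appear as a confounder. The article also names the unadjusted tests for these outcomes outright, so this is a stated choice and not merely an omitted detail.

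A reader might infer more: that the standard error is certainly too large, that the reported intervals will be wrong, or that a deliberate precision gain is being thrown away. The document supports none of these. The first two depend on a college difference for which it gives no figure. As to the third, it states no purpose for the separate lists.

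**Conclusion.** The mismatch between stratified allocation and unstratified tests is clear from the text. Its consequence is conditional: a loss of precision in the conservative direction that grows with the difference between colleges and vanishes if there is none. At the protocol's own effect and 50 per arm, the cost is about 2 points of power or less for R² up to 20%, and power exceeds 90% either way. It matters more if losses bring the trial down to about its planned minimum, where the cost reaches roughly 6 points at R² of 20%.

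These figures rest on an assumed R², normally distributed scores with equal variances, and balance within college carrying through to the analysed set. The estimate is not biased by the omission, type I error is not inflated, and the sample size stands. This is a near-free improvement, not a flaw that threatens the trial's conclusions.

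**What to change.** In the Statistical analysis section, make the primary comparison of PSS, and the comparison of PSQI, a linear model with arm and college as fixed factors, and say that college enters because it is the randomisation stratum. Keep this separate from the conditional clause on confounders, so that including it does not depend on the data. Wherever a rank test is used to compare the arms, replace the plain Mann-Whitney test with a college-stratified (van Elteren) test.

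The cost is one model term and one degree of freedom. College is already known for every participant from the allocation lists, so data collection, conduct and sample size do not change.

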### Blinding

Due to the nature of the study, the existence of the two arms in the experiment cannot be concealed (this will be a study limitation), but some levels of blinding will be considered. For example, the participants on each arm will not be informed about what the other arm will receive.

### Procedures

All the participants will fill out the demographic data and other study questionnaires electronically. Then, the researcher will send a link to the intervention group to have access to the stress management app (Naranj) and another link to the control group to download an app unrelated to stress management.

The Naranj app includes a user profile, stress management strategies, consultation requests, and COVID-19 sections. The user profile includes account data, demographics, and health history (nutrition, physical activity, smoking, diseases, drug and alcohol consumption, etc.). Stress management strategies are based on the Acceptance and Commitment Therapy (ACT), Stress Reduction Theory (SRT), and some other evidence-based strategies. This section consists of various parts, including metaphors based on ACT, 4-7-8 breathing technique, Emotional Freedom Technique (EFT), pictures of nature, relaxing music, relaxing videos, educational quotes, my diary, forum, and meditation. In “my diary,” students have a space to enter their thoughts, emotions, and experiences of using the strategies. The “consultation request” section provides users with the opportunity to use emergency (receiving service during 24 h) and usual (receiving service during 48 h) consultations with psychological consultants. The “COVID-19” section provides educational content on COVID-19. In addition, this section is hyperlinked to the “stress management strategies” section. The Naranj app includes “privacy policy and terms of use,” app tutorial, contact us, and frequently asked questions, as well.

An app regarding calorie uptake management will be offered to the control group. This app is comparable to the Naranj app in terms of the need for daily use by the user. However, it is different from Naranj in terms of content. The rationale for using this app is to determine whether there will be an improvement in the outcome measures due to the stress management content in the Naranj app. Overall, both groups are provided with the same conditions. In this way, the effect of the confounding factors, if any, can be controlled and the Hawthorne effect will be minimized. According to the Hawthorne effect, individuals will alter their behaviors in response to being studied and usually refer to positive changes [42].

Both groups will have access to their specified apps for 3 months. All participants in the intervention and control groups will be requested to complete the questionnaires again after completion of the intervention.

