### Data collection

The participants will be asked to fill out three electronic questionnaires. At baseline, they will be asked to complete the demographic information form, Perceived Stress Scale (PSS), and Pittsburgh Sleep Quality Index (PSQI). After the completion of the intervention, they will be requested to complete the PSS and PSQI again (Fig. 1). Since the Iranian government has advised the public to minimize face-to-face interactions and isolate themselves at home during the COVID-19 pandemic, the electronic versions of the questionnaires will be used. Information on the app use, such as daily stress level and daily quality of sleep measured daily using the visual analog scale (VAS) in the web app, as well as the frequency of using different app sections will be collected, as well. Data on the app use and the possible use of other apps, including apps related to stress management, will also be collected.

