## Discussion

This study aims to develop a web application and to determine its impact on stress management among college students. Development of the suggested web application and evaluation of its impact on the students will have the potential to develop useful media for managing stress, improving sleep quality, and providing information about the effectiveness of stress management strategies among college students who have been shown to experience high-stress levels. It has been hypothesized that the web application can reduce the stress level and improve the sleep quality among the target college students. It will also promote students’ healthy behaviors. Considering the fact that mental health services are limited in developing countries, many people cannot access fair resources, and only few applications developed in this field are evidence-based. Therefore, this theory-based web application is expected to be a promising tool to help students in Iran. To avoid the risk of contamination between the intervention and control groups, the web application will be available only to the intervention group by putting all intervention group participants in a white list and registering them in the web application. Then, web application registration will be disabled temporarily during the intervention, so that it cannot be used by anyone else. Overall, the study results will indicate an important step towards developing a technology platform for delivering a range of psychosocial strategies for managing stress and sleep problems.

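### The calorie-app control matches Naranj on daily use, but not on consultant access or daily self-rating, so the trial can credit the whole package and not the stress-management content alone

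*Protocol article*

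**What the plan says.** The Procedures section of the protocol article gives the control group a calorie-management app. It names one app feature on which the two are comparable, that each has to be used every day, and says they differ in content. The stated purpose is to learn whether there is "improvement in the outcome measures due to the stress management content in the Naranj app". It then concludes: "Overall, both groups are provided with the same conditions". From this it draws two consequences: confounding factors can be controlled, and the Hawthorne effect will be minimised.

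The same section lists four parts of Naranj: user profile, stress-management strategies, consultation requests and a COVID-19 part. The consultation part offers "emergency (receiving service during 24 h) and usual (receiving service during 48 h) consultations with psychological consultants".

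The Data collection section adds that the usage information includes "daily stress level and daily quality of sleep measured daily using the visual analog scale (VAS) in the web app", together with how often each app section is used. The Discussion says that only intervention participants can register for the web application, to prevent contamination.

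**The concern.** The rationale credits the control app with a property that the described design does not have. An attention control isolates content only if everything else that could move the outcome is alike in both arms. Here at least two such elements are described for one arm only: contact with a professional, and a daily prompt to rate the two constructs that the trial measures as outcomes.

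What is at stake is the interpretation of a positive result. A report that follows the Procedures rationale would credit the stress-management content. A lower Perceived Stress Scale (PSS) score in the Naranj arm could equally reflect access to a consultant or the effect of daily self-rating, and the data could not tell these apart.

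**Working it through.** **Is a figure involved?** No figure in the plan is disputed. The sample size was reproduced only to confirm that it is unaffected.

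- Inputs (Sample size section): "the mean (SD) of perceived stress in groups 1 and 2 were 7.43 (2.93) and 9.49 (3.06), respectively", 80% power, α = 0.05.
- Difference: 9.49 − 7.43 = 2.06. Pooled SD: √((2.93² + 3.06²)/2) = 2.996. Standardised difference: 2.06/2.996 = 0.688.
- The two-sided two-sample t test needs 34.18 per group, rounded up to 35, as stated. Power at 35 per group is 0.81.
- Allowance for loss: 35/(1 − 0.30) = 50 per group, as stated.

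None of this depends on which component of Naranj produces an effect.

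**What is matched and what is not**

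| Element | Naranj arm | Control arm | Where stated |
|---|---|---|---|
| Daily use needed | Yes | Yes | Procedures |
| Access time | 3 months | 3 months | Procedures |
| PSS and Pittsburgh Sleep Quality Index (PSQI) at baseline and end | Yes | Yes | Data collection |
| Psychological consultants, within 24 h or 48 h | Yes | None described | Procedures |
| Daily stress and sleep ratings on a visual analogue scale (VAS) | In the web app | No access to that app | Data collection, read with Discussion |

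The first three rows support a statement of partial matching. The last two contradict the statement of equal conditions. The consultant row needs no inference about what counts as content, because the protocol lists consultation requests apart from the strategies. The VAS row rests on two sections read together: one places the ratings in the web app, and the other closes that app to the control group.

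**What the contrast identifies.** As a simple additive sketch, write the expected between-arm difference as

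Δ = content effect + consultant-access effect + daily-rating effect.

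Two arms give one estimate, Δ, and there are three unknown terms on the right. Any split is compatible with the same Δ, so the content term is not identified. Allowing the elements to interact only adds unknowns. Δ itself is estimated validly by the randomised comparison.

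**The two consequences drawn in Procedures**

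- *Confounding.* Randomisation balances baseline factors in expectation. The protocol, however, rests control of confounding on the equality of conditions. Consultant access and daily rating arise after randomisation, by arm, so randomisation does not remove them from the content comparison.
- *Hawthorne effect.* The protocol describes this as people changing because they are being studied. Giving both arms an app and the same questionnaires does reduce a difference from that source. Daily rating of stress and sleep in one arm adds self-observation there, so the claim is not secured.

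**The case against.** The strongest reply is that the trial already aims at the package. Aims and objectives speaks of the efficacy of the web application, and the Background hypothesis is also about the application as a whole. If the content of Naranj is read as everything Naranj contains, the attribution sentence becomes a package claim. Procedures itself says the apps differ in content, and it says the Hawthorne effect is minimised, not removed. Most of this stands: the design, outcomes and tests need no change. It does not rescue the statement of equal conditions, which fails on either reading for consultant access and daily rating.

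A reader might also infer several stronger points that the documents do not support:

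- *The forum as a further unmatched element.* The protocol lists it inside the stress-management strategies, so it is part of the content. The calorie app's features are not described, so its absence there would be a guess. Likewise, the COVID-19 part is educational material linked to the strategies, and the point does not need it.
- *A claim about each separate strategy.* The Discussion hopes for "providing information about the effectiveness of stress management strategies among college students". That can be read collectively, and it is worded as a potential.
- *Use of the daily VAS as evidence between arms.* Data collection treats it as app-use information, and Outcomes names only the PSS and PSQI.
- *A plan to offer the app without consultants.* No section says so.
- *An inflated false-positive rate from expectation in an open trial.* The Blinding section already calls the lack of concealment a limitation and mitigates it in part by not telling participants what the other arm receives. Any size put on this would be assumed, and it would measure a different problem. If consultations lower stress, that is a real effect of the application and not a false positive.

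**Conclusion.** The concern holds for the rationale in Procedures. The arms are matched on daily use, access time and the PSS/PSQI assessments. As described, they are not matched on consultant access or daily self-rating. The trial can estimate the effect of the whole Naranj package against a calorie app, and it cannot attribute benefit to the stress-management content alone.

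The size cannot be put as a number. The share of any effect due to content is not identifiable from two arms, and no estimate, test or sample size changes. It would be wrong to conclude that the randomised comparison is invalid, because it answers the stated aim.

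The verdict assumes that the control group receives neither consultant access nor a daily stress and sleep rating by another route. The article describes none. If the full protocol provides either one, the corresponding part of the point falls away.

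**What to change.** 1. In Procedures, replace the statements on equal conditions, the Hawthorne effect and attribution to content. Say instead that the arms are matched on daily use, 3 months of access and the PSS/PSQI assessments, and that they differ in access to psychological consultants and in daily self-rating of stress and sleep.
2. Limit the conclusion to the effect of the Naranj package, including those two elements, compared with a calorie app. Aims and objectives can stay as written.
3. Report how many intervention participants used consultations, from the section-use data already planned under Data collection. Present this as description: use is chosen after randomisation, so comparing users with non-users would not isolate the effect of consultation.

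The cost is a few sentences and one line in a table, with no new data and no change to design, sample size or analysis. The downside is a narrower claim than the present rationale makes.
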